### Statistical Analysis

#### Overview

For the comparison of a 12-month change in minutes per week of MVPA from baseline between the intervention and control groups, a 2-sided, 2-sample 2-tailed *t* test with a significance level of .05 (or a nonparametric approach such as the Wilcoxon rank sum test if parametric assumptions fail) will be conducted. In general, analyses will incorporate the intention-to-treat principle, which includes all participants who are randomized in the analysis. A mixed model for repeated measures (MMRM) will also be considered. The dependent variable in the MMRM is the change from baseline in minutes per week of MVPA at each postbaseline visit (6 and 12 months). Independent variables in the MMRM include study arm, visit (as a categorical variable), arm-by-visit interaction, minutes per week of MVPA at baseline, and potential covariates of interest (eg, baseline BMI, sex, age, ethnicity and race, marital status, parental status, employment status, and smoking status) that are determined a priori. Potential covariates significantly associated with outcome (*P*<.10) will be included in a multivariable logistic regression model. To avoid inflation of the type I error, we will use permutation tests for inference. Missing data will be evaluated. If the missingness is not random (nonignorable), multiple imputation or propensity weighting will be considered. There will be no planned interim analyses for efficacy or futility conducted for this study. In addition, a frequency table comparing the arms in terms of meeting the guidelines (dichotomized as *yes* or *no*) will be created, and a Fisher exact test will be conducted. Furthermore, a generalized estimating equations regression will be conducted with meeting the guidelines (*yes* or *no*) as the dependent variable and visit, arm, and visit by arm as interaction terms in the model using an appropriate correlation structure adjusted by similar covariates to those of the primary aim. Statistical analyses will be conducted using the statistical software R (version 4.1.2).

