#### Power Considerations

Our sample size (N=386) provides sufficient power for our primary aim. On the basis of a 2-sided, 2-sample *t* test, with a sample size of 193 in each arm (386 participants in total) and a type I error (α) of .05, we achieve 80% power to detect a standardized effect size [1-3,8,9] of 0.32 for comparing a month 12 change from baseline in minutes per week of MVPA between arms, accounting for an attrition rate of 20% in measurement (ie, completing the ActiGraph measurement battery at 12 months but not necessarily adhering to the use of the DHI; Table 2). We have powered for a 0.32 effect size, through which we anticipate a change from baseline of 45 minutes of MVPA after 12 months in the control arm and a 75-minute change from baseline in MVPA for the intervention arm assuming a pooled SD of change of 94 minutes and a mean change score difference of 30 minutes per week of MVPA.

**Table 2 table2:** Sample size and power (2-sided α=.05).

Power	Effect size	Sample size per group	Overall sample size	Overall sample size considering 15% attrition	Overall sample size considering 20% attrition
0.8	0.32	154	308	362	386
0.8	0.36	122	244	288	306
0.8	0.4	99	198	234	248
0.85	0.32	176	352	414	440
0.85	0.36	139	278	328	348
0.85	0.4	113	226	266	284

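### The missing-data rule is the wrong way round: imputation or weighting is reserved for nonignorable missingness, and no method is committed for the ignorable case

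*Protocol article*

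**What the plan says.** All the relevant statements are in the protocol article, under Statistical Analysis.

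- **Primary comparison** (Overview). A two-sample t test, or a rank-sum test if parametric assumptions fail, is named "For the comparison of a 12-month change in minutes per week of MVPA from baseline between the intervention and control groups".
- **Population** (Overview). "In general, analyses will incorporate the intention-to-treat principle, which includes all participants who are randomized in the analysis".
- **MMRM** (Overview). "A mixed model for repeated measures (MMRM) will also be considered". Its outcome is change from baseline at 6 and 12 months, with arm, visit, their interaction and baseline MVPA as terms.
- **Missing data** (Overview). There are two sentences: "Missing data will be evaluated", and then "If the missingness is not random (nonignorable), multiple imputation or propensity weighting will be considered". No method is named for ignorable missingness, and the MMRM is not linked to missing data.
- **Sample size** (Power Considerations). The t test is powered "with a sample size of 193 in each arm (386 participants in total) and a type I error (α) of .05", "accounting for an attrition rate of 20% in measurement". Table 2 shows 154 per arm (308 in total) before inflation and 386 after it.

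**The concern.** The rule has two branches, and neither does its job.

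**Nonignorable branch.** Standard multiple imputation draws the missing values from a model fitted to the observed data. Propensity weighting reweights the observed participants by their modelled chance of being observed. Both rest on MAR, and the plan calls on them exactly where MAR fails. The parenthetical gloss makes it hard to read the sentence as loose wording for data that are merely not missing completely at random. The trigger also cannot be evaluated: observed data do not distinguish MAR from nonignorable missingness, so the choice would be a judgement made once the data are in hand.

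**Ignorable branch.** Nothing is committed. A change-score t test without imputation has no value for a participant without a 12-month ActiGraph measurement, so that participant drops out of the primary comparison. MAR is the situation in which imputation, weighting or the MMRM would help.

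At stake is the primary estimate. If dropout depends on progress differently in the two arms, the difference among completers is not the difference among those randomized. Differing dropout is possible here: only YourMove has the daily EMA and the Reflect tool (Table 1).

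**Working it through.** **1. Reproduce the plan's own figure.** Inputs from Power Considerations: standardized effect 0.32, two-sided α 0.05, power 80%, attrition 20%.

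- n per arm = 2 × (1.960 + 0.842)² / 0.32² = 153.3, rounded up to 154. Table 2 agrees.
- Power of the t test at 154 per arm is 0.799.
- 154 / 0.80 = 192.5, rounded up to 193 per arm, or 386 in total. Table 2 agrees.

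The power statement therefore rests on 308 participants with the endpoint. At the planned attrition, 386 − 308 = 78 randomized participants would have no 12-month value.

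**2. Set the rule beside the methods.**

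| Missingness judged to be | What the plan commits to | Position |
|---|---|---|
| Ignorable (MCAR or MAR) | No method | The t test uses those with 12-month data; valid under MCAR, can be biased under MAR |
| Nonignorable | Imputation or weighting to be considered, form unstated | In standard form, assumes the MAR condition just rejected |

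**3. Size of the effect, as an illustration.** From the documents: 193 per arm, mean changes 75 and 45 (difference 30), SD 94. Assumed, because the documents do not give them: the same means and SD at month 6, the 6-to-12-month correlation, and the dropout model.

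*Independent check* (2,000 simulated trials, correlation 0.6, about 20% missing overall). Control dropout is random. YourMove dropout has log-odds −1.6 − 1.0 per SD of response, except in the MCAR row.

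| Mechanism | Completers' difference | Imputing from month 6 |
|---|---|---|
| MCAR | 30.0 | 29.9 |
| MAR (depends on observed month-6 value) | 40.1 | 30.1 |
| Nonignorable (depends on unseen month-12 value) | 46.6 | 41.0 |

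Under MAR, where the rule does not call for imputation, imputation removes a bias of 40.1 − 30 ≈ 10 min/week. Under nonignorable dropout, where the rule does call for it, 41.0 − 30 = 11 min/week remains.

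*Range under MAR* (correlation 0.6, large samples; the slope is the fall in log-odds of dropout per minute of 6-month gain).

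| Dropout assumption | Completers' difference |
|---|---|
| Slope 0.012 in both arms, 20% / 20% | about 30 |
| Slope 0.012 in both arms, YourMove 25% / control 20% | about 32 |
| Slope 0.003 in YourMove only, 25% / 20% | about 34 |
| Slope 0.006 in YourMove only, 25% / 20% | about 38 |
| Slope 0.012 in YourMove only, 25% / 20% | about 43 |

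A slope of 0.012 is strong: exp(0.012 × 94) is an odds ratio of about 3.1 per SD. With response-dependent dropout in YourMove only, correlations of 0.4 to 0.6, slopes of 0.004 to 0.012 and YourMove loss of 20% to 25%, the completers' difference ran from 32.5 to 42.9. A model using the 6-month value gave 29.5 to 30.4 throughout.

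**The case against.** **A MAR-valid analysis is already in the paragraph.** This stands in part. The MMRM is likelihood-based and uses partial follow-up, so a reader should not infer that the plan has no MAR-valid method. But it is only to be considered, it is not the primary comparison, and the missing-data rule does not point to it.

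**Imputation can serve nonignorable missingness.** True of versions with an explicit nonignorable model, such as delta adjustment or pattern mixtures. The article names none, and that detail could sit in an analysis plan that is not shown. The reversed pairing would still have to be overturned there, not merely expanded.

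**Inflating for attrition does not define an analysis population.** This stands. A reader might infer that the sample-size section itself excludes 20% and so contradicts intention-to-treat. It does not: inflation is compatible with imputation or an MMRM. The conflict lies between the statement that the analysis "analyses will incorporate the intention-to-treat principle, which includes all participants who are randomized in the analysis" and a change-score t test with no committed imputation. The attrition figure only shows how many participants that could affect.

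**Dropout need not differ by arm.** Power Considerations separates completing the ActiGraph measurement from using the intervention. Visit payments are equal across arms, and both arms receive check-ins to support measurement. These features make differential loss less certain, and with the same mechanism and rate in both arms the bias is about zero. They do not rule it out, and the plan's attrition evidence covers only 3 months (5%) and 4 months (11%).

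**Conclusion.** The point holds on the published text. The rule is wrong as stated, not merely brief: it assigns standard MAR methods to the nonignorable case, uses a trigger that observed data cannot settle, and commits nothing for the ignorable case.

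The size is conditional. Across the assumed MAR scenarios the completers' difference overstates a true 30 min/week by about 0 to 13. The upper end needs strong response-dependent dropout confined to YourMove. It is tempting to say that the primary t test is biased, but the documents support only that it can be, mainly when dropout depends on response differently by arm. They give no correlation, dropout model or arm-specific attrition, so no single figure should be read as the expected bias.

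**What to change.** Replace the missing-data sentence with three commitments.

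1. **Primary estimate.** Whatever mechanism is judged to apply, take it from a MAR-valid analysis of all randomized participants. Either commit to the MMRM already described, with the arm difference at month 12 as the estimate, or use multiple imputation within arm from baseline and 6-month ActiGraph MVPA, with Fitbit MVPA as an auxiliary variable if wished. If the MMRM is chosen, say how participants with no post-baseline measurement are handled, since they supply no outcome to it.
2. **Nonignorable missingness.** Treat it as a sensitivity question, not a trigger: delta-adjusted or return-to-baseline imputation, varied by arm.
3. **Completers' t test.** Keep it as a supportive analysis, labelled as using participants with 12-month data.

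The cost is wording and some programming. The enrolled 386 is unchanged. The Results section says data collection was still under way and analysis had not begun at publication, so the change could be fixed before any arm comparison is run.

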#### Power Considerations

Our sample size (N=386) provides sufficient power for our primary aim. On the basis of a 2-sided, 2-sample *t* test, with a sample size of 193 in each arm (386 participants in total) and a type I error (α) of .05, we achieve 80% power to detect a standardized effect size [1-3,8,9] of 0.32 for comparing a month 12 change from baseline in minutes per week of MVPA between arms, accounting for an attrition rate of 20% in measurement (ie, completing the ActiGraph measurement battery at 12 months but not necessarily adhering to the use of the DHI; Table 2). We have powered for a 0.32 effect size, through which we anticipate a change from baseline of 45 minutes of MVPA after 12 months in the control arm and a 75-minute change from baseline in MVPA for the intervention arm assuming a pooled SD of change of 94 minutes and a mean change score difference of 30 minutes per week of MVPA.

**Table 2 table2:** Sample size and power (2-sided α=.05).

Power	Effect size	Sample size per group	Overall sample size	Overall sample size considering 15% attrition	Overall sample size considering 20% attrition
0.8	0.32	154	308	362	386
0.8	0.36	122	244	288	306
0.8	0.4	99	198	234	248
0.85	0.32	176	352	414	440
0.85	0.36	139	278	328	348
0.85	0.4	113	226	266	284

To develop this power calculation, we examined effect sizes from 3 different studies available at the time of study design [26] plus our own previous formative research results [93,95-98] to establish an effect size of 0.32 as reasonable. When combined, previous studies and formative research results address power considerations related to using similar measurement batteries, detecting meaningful effects at 12 months between 2 active interventions and plausibly meaningful effects to be anticipated when comparing our YourMove intervention approach to our active control. First, these estimates are consistent with those of the study by Lynch et al [98], which we used as a reference as it conforms to effects that we observed in our formative research. It evaluated a technology-based intervention and used a similar measurement protocol, particularly an ActiGraph monitor, to assess minutes per week of MVPA. That said, the trial did not assess differences at 12 months, nor did it compare 2 active interventions. As such, we used the Community Health Advice by Telephone trial as a second reference, whereby an effect size of 0.32 (ie, the same effect size as that for our study) was also observed as the difference between 2 active and successful PA interventions at 12 and 18 months after baseline, with one being a technology-based intervention and the second being a human-based intervention [97,99]. As our RCT includes an active goal-setting intervention, we also examined effect sizes in a third trial by previous studies [95,96]. Specifically, Adams et al [95] conducted a trial comparing adaptive step goals to static step goals (ie, 10,000 steps per day) and also immediate reward provision versus delayed reward provision (with both groups, similarly to ours, receiving gift cards if they met a daily step goal target). Results indicated that all conditions significantly increased by, on average, 2389 steps per day over 4 months (which aligns with our pilot study of JustWalk version 1 of 2651 steps per day [100] at 3 months). Results further indicated a significant difference at intervention completion favoring immediate over delayed reward (with immediate reward in alignment with our protocol) and an effect size of 0.32 comparing these 2 active interventions. The condition most similar to our intervention condition (ie, adaptive goals+immediate feedback) exhibited gradual increases in steps across the intervention, including until study end, which supports our assertion of the value of gradual habit formation. In our pilot study, we had 5% attrition over 3 months, and the study by Adams et al [95] had an attrition rate of 11% at 4 months. On the basis of this, our oversampling to support up to 20% attrition at 12 months is justifiable, particularly when considering the use of the ActiGraph monitor for assessment instead of using a measurement approach that is linked to the intervention in some way. In summary, based on the overall state of the science, being able to detect an effect size of 0.32, which equates to a change difference of 30 minutes per week of MVPA between YourMove and the active control via ActiGraph at 12 months, would illustrate both a clinically meaningful difference and also a difference that is conservative enough to be observable between 2 active interventions based on prior work.

## Results

The YourMove study was funded in July 2020 and received institutional review board approval on July 1, 2020. Recruitment and enrollment began in October 2022, and a total of 386 participants were enrolled by August 2024. Data collection is ongoing and expected to conclude by August 2025. Data analysis has not yet begun, and results are anticipated in early 2026.

## Discussion

### Overview

Our prior work has emphasized the need for personalized interventions that can adapt dynamically to each individual’s evolving context and behavioral patterns. We observed that internal factors (eg, stress and busyness) and external factors (eg, the weather and day of the week) influence PA in ways that vary not only across individuals but also within individuals over time. These findings align with and extend previous research showing that DHIs for PA tend to yield moderate short-term effects and are generally acceptable, yet their benefits often diminish over time and are typically limited to specific subpopulations. Together, this evidence underscores a critical gap in current intervention design—the need for approaches that are responsive to the inherently dynamic and idiosyncratic nature of PA rather than relying on static behavior change assumptions.

To address this gap, the YourMove DHI integrates two core components: (1) habit formation mechanisms driven by the team’s proposed COT approach and (2) knowledge, skill, and practice development components via a self-experimentation approach modeled after the Schraefel et al [48] experiment in a box (XB) approach to improve MVPA. There are many potential contributions of this work. First, our intervention is the first scaled deployment and testing of the team’s overall COT approach, described previously. Designed to be highly scalable for improving behaviors and reducing chronic disease risk, if effective, it could be used widely through smartwatch and smartphone technology. In addition, this study will be a rigorous evaluation of the COT approach via an RCT. If our approach to offering personalized and perpetually adaptive support is helpful for PA, it will provide justification for extending the approach to other health behaviors that are dynamic and idiosyncratic, such as weight loss or addiction.

### Previous Research That Informed Our COT Element

As a proof of concept for the COT approach used in YourMove, system ID techniques were used to develop an idiographic dynamic model using participant data from the team’s previous study, Just Walk [89], which included an intervention aimed at promoting walking behavior among sedentary adults. While YourMove builds on foundational insights from Just Walk, it represents a deliberate and planned expansion of the original work. Notably, this protocol includes a broader age range (adults aged ≥25 years) and is not limited to individuals who are overweight or obese, as was emphasized in earlier protocol versions and peer-reviewed materials. These changes were implemented in response to iterative design work that was explicitly outlined in the funding grant and intended to enhance generalizability and future scalability. In addition, while both studies center on mobile health–based PA promotion, YourMove incorporates new components, including a knowledge, skill, and practice self-experimentation element and broader COT infrastructure to support real-time N-of-1 adaptation that is both guided by the controller and self-guided. These deviations from the original protocol are intended to enhance generalizability and reflect iterative improvements informed by the design work that was part of the funding grant.

On the basis of this formative work, we conducted a number of analyses intended to lead to more predictive models that informed intervention development and decision policies for a personalized and perpetually adapting intervention. The estimated model was subsequently used to evaluate a control-oriented decision-making algorithm designed for an adaptive DHI that promotes PA in sedentary adults within a simulation environment [89]. The decision-making framework was based on 3DoF-KF HMPC formulation, incorporating a mixed logical dynamic framework to represent categorical and logical decisions within the policy. A three-degree-of-freedom tuning approach was implemented, allowing for independent adjustments for response speed to set point tracking and disturbance rejection, both measured and unmeasured. Simulation results highlighted the integration of system ID and the HMPC controller formulation, demonstrating the potential for optimal and personalized PA interventions—a crucial step toward large-scale dissemination of behavioral interventions for PA promotion. The estimated model displayed strong predictive capabilities while maintaining a good fit to the data. This model was used as the predictive component in simulations to assess the efficacy of the 3DoF-KF HMPC framework in delivering individualized PA interventions. Simulation outcomes showed the HMPC algorithm to be highly effective in guiding personalized PA interventions. In addition, within the HMPC algorithm, the controller was reconfigured to support a maintenance phase, reducing or eliminating financial incentives to help participants sustain healthy PA levels without dependence on rewards [48].

Thus, the YourMove study described in this protocol is the logical next step in this systematic line of research meant to develop ways to use control systems engineering methods to guide the creation of personalized and perpetually adaptive interventions. The results of this trial will provide a robust nomothetic test of the value of the many decisions and efforts of the team to create a robust operationalization of this type of personalized and perpetually adapting intervention. Significant results suggesting improvements in MVPA relative to an active control will provide compelling evidence for both digital health and digital therapeutics companies to consider incorporating this algorithmic approach into their tools. In addition, these results will provide justification for the continued development and expansion of the use of control systems engineering approaches for providing highly personalized and perpetually adaptive interventions for individuals, thus filling a critical gap in care, namely, the capacity to provide the “right” type of support that is appropriate for each person over time.

### Previous Research Informing Our Self-Experimentation Tool

The Reflect tool was based on the XB framework developed by Schraefel et al [48]. Contrary to common digital health tools that seek to provide the solutions for participants, the XB approach allows participants to experiment with general health heuristics to discover what is useful for themselves. Through self-experimentation, an individual can build knowledge, skills, and practice to transform a general health heuristic (eg, national guidelines for PA) into a personal health heuristic (eg, a regular exercise routine that adapts to different contexts) [48]. Aligned with self-determination theory, the XB framework gives a participant the opportunity to develop autonomy to determine and use strategies that work for them without pressure to adopt ones that are not useful [100]. In this way, participants are the agents of achieving desired behavior change rather than the intervention or technology itself.

This work also aligns with other frameworks of self-experimentation such as the personal science framework [101] and self-study [102]. Personal science is illustrated by a cycle of five activities in which individuals examine their personal health by (1) *asking questions* unique to their health status and behaviors; (2) *designing* to discover and apply necessary changes; (3) *observing* to self-track meaningful data; (4) *reasoning* to reassess questions, designs, and observations; and (5) *discovering* what is helpful or needs further questioning [101]. Similarly, self-study involves experimentation and tracking at an individual level to establish autonomy and make meaningful impacts on one’s health [48]. By using the XB and personal science frameworks and self-study, Reflect is a tool in the YourMove intervention designed to promote intrinsic discovery of personal PA health heuristics to enable resilient PA practice.

While this intervention component was a secondary element to the overall intervention, if our trial results suggest significant differences in our active intervention relative to the control, it will provide empirical justification for continued study and exploration on ways in which self-experimentation approaches can be developed within digital health and digital therapeutics tools. We see particular value in this approach as a strategy for ensuring the ethical use of these digital technologies via an explicit incorporation of the person determining whether an intervention is working for them based on their own self-experiments.

